### Sample size calculation

To ensure that the study is adequately powered for the primary outcome, we have calculated the minimum required sample size, which we have also adjusted for a 10% expected information loss and multiple comparisons. To maintain the global significance level alpha at 0.05, for the sample size calculations, we decreased the significance level for the univariate analyses to 0.01 per Bonferroni correction. As we aim to capture predictors with significant influence on clinical remission, we set the effect size of the primary outcome at 25%. In order to detect a 25% or higher difference between the compared groups, as defined by disease characteristics and therapy induction types and considering the variable sampling ratio (2:1 to 1:2 depending on the factor), we will need 203 patients with CD and 214 patients with UC/IBD-U. Considering approximately 40% of PIBD diagnoses comprises UC/IBD-U, we will need 535 patients with PIBD. Subsequently, the CD group will have slightly increased power than the originally planned 80%.

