**Activity**								
Study explained, informed consent	X							
Collection of routine clinical and laboratory data, including faecal calprotectin	X	X	X	X	X	X	X	X
Extra blood sample taken at time of routine blood draw (maximum of 20 mL)*****	O	O	O	O	O	O	O	O
Extra biopsies taken at time of clinically required colonoscopy (maximum of 8)*	O							O
Tissue sample in case of indication for surgical resection*		O	O	O	O	O	O	O
Environmental questionnaire	X							
IMPACT III and EQ-5D questionnaires	X (both)		X (EQ-5D)	X (EQ-5D)	X (both)	X (EQ-5D)	X (both)	
School attendance and WPAI questionnaires	X (both)		X (both)		X (both)		X (both)	

*This activity will only be performed in patients included in the subcohort. ‘X’ is performed in all patients, ‘O’ is only performed in patients included in the subcohort.

WPAI, Work Productivity and Activity Impairment.

At least 535 patients with PIBD need to be included in the inception cohort. However, since this is an observational study, depending on the feasibility, the study will aim to recruit 1000 patients. In specific centres with the capacity to perform immunological analyses, participants are included in a subcohort for additional collection of biological specimens. This allows in-depth characterisation of immunological pathways in 100 patients with CD and 50 patients with UC and provides the opportunity to relate predictive factors to underlying immune dysfunction during follow-up. The inception cohort is part of the PIBD-SETQuality project, which is funded by Horizon 2020.

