### Analysis and statistical methods

Data analysis will be performed with SPSS V.26 or higher for Windows and R version 3.6 or higher (R Foundation for Statistical Computing, Vienna, Austria). Descriptive statistics will be computed overall and per disease (CD and UC). Phenotypic grouping will be performed according to specific disease characteristics (eg, age of onset, disease localisation and disease behaviour). Next to this, patients will be categorised according to treatment categories. The appropriate descriptive statistics will be used to summarise the demographic characteristics. The primary outcome will be analysed using a 2-proportion Z test for the comparison of the different groups in our sample, using a stricter confidence level of 0.01 per Bonferroni correction. All proportions will be summarised per group, and 95% CIs will be provided. The important factors from the univariate analysis will be used to build a generalised linear model with a logit link function. This will be a multiple analysis of the effects that the selected factors and covariates have on the outcome of clinical remission. The final model will also include interaction terms, if necessary, and will be optimised based on fit diagnostics and residual analysis. The same approach will be used for the secondary outcomes of clinical remission. We will use a mixed-effects linear model to study the effects of the predictors on the disease activity index over time, taking into account the non-independence between the observations due to the repeated measurements from each patient. For the additional long-term secondary outcomes that have a time-to-event nature, we will use Kaplan-Meier curves to summarise the effects of the categorical factors on the outcome. This will be used to build a Cox regression model with the important factors and covariates that have a significant effect on the time and frequency of the events as defined in the outcomes section.

Similar methods will be used for the analysis of the exploratory outcomes. For these outcomes, propensity scores and multivariate methods are required, in particular for the immunological data, including principal component, factor and cluster analysis. Incidences of serious adverse events (SAE) and the SAE rate per 100 patient-years will be calculated. Missing data analysis will be performed based on the missing at random or missing completely at random mechanisms. Emerging patterns will be thoroughly examined.

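### The protocol calls the power gain in Crohn's disease slight, but its own numbers imply about 96% power rather than just over 80%

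*Protocol article*

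**What the plan says.** In *Sample size calculation*, the protocol article states that "we set the effect size of the primary outcome at 25"%, as a difference between compared groups in clinical remission at 1 year. The calculation is "adjusted for a 10% expected information loss and multiple comparisons". For the latter, "we decreased the significance level for the univariate analyses to 0.01 per Bonferroni correction". Group sizes are allowed to be unequal, "considering the variable sampling ratio (2:1 to 1:2 depending on the factor").

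On that basis, "we will need 203 patients with CD and 214 patients with UC/IBD-U". Taking UC/IBD-U as roughly 40% of diagnoses, the section arrives at 535 patients in total. It then adds that "the CD group will have slightly increased power than the originally planned 80"%. No number is attached to the increase.

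*Study design* treats the total as a floor ("At least 535 patients with PIBD need to be included in the inception cohort") and names 1000 as the aim if feasible. *Analysis and statistical methods* confirms the test: "The primary outcome will be analysed using a 2-proportion Z test for the comparison of the different groups in our sample".

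**The concern.** The disease with the smaller share sets the total. Once the total is scaled up to secure enough UC/IBD-U patients, the CD group becomes much larger than it needs to be. The section acknowledges a gain in CD power but describes it as slight, which is a statement about size that its own figures can test.

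This sentence is the only one in the article that describes power in the larger disease group for the primary outcome. A reader weighing a non-significant CD predictor would take from it that a real 25-point difference had nearly a one-in-five chance of being missed. If power is in fact well above 90%, a null CD result is considerably more informative than the article suggests.

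**Working it through.** **Inputs from the protocol article.** Alpha 0.01 per comparison; planned power 80%; target difference 25 points; sampling ratio 2:1 to 1:2; 10% information loss already included; 203 CD and 214 UC/IBD-U required; UC/IBD-U share about 40%; total 535.

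**Not stated, so assumed.** Sidedness (two-sided, with one-sided also tried) and the reference remission rate (lower-group rate varied from 5% to 70%).

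**Step 1: reproduce the total.** 214 / 0.40 = 535. The figure reproduces exactly.

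**Step 2: CD patients within that total.** 0.60 × 535 = 321. Surplus over requirement: 321 − 203 = 118, and 321 / 203 = 1.58, so 58% more. Both figures are before the 10% loss, so the ratio is unchanged among evaluable patients.

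**Step 3: can 203 and 214 be reached?** Yes, with a pooled two-sided Z test and 10% loss taken as N / 0.9:
- 31% v 56% at 1:1 needs 182 evaluable; 182 / 0.9 rounds up to 203.
- 22% v 47% at 2:1 needs 192 evaluable; 192 / 0.9 rounds up to 214.

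Other combinations also reach these figures. The protocol's rates are unknown, so this shows only that neither number is contradicted.

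**Step 4: CD power at 321, taking 203 = 80% as given.** For a fixed difference, the standardised effect grows with the square root of N:

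power = Φ[(z_α + z_0.80) × √(321/203) − z_α]

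- Two-sided 0.01: (2.576 + 0.842) × 1.2575 − 2.576 = 4.297 − 2.576 = 1.722, so power is 95.7%.
- One-sided 0.01: (2.326 + 0.842) × 1.2575 − 2.326 = 1.657, so power is 95.1%.

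**Step 5: direct check without the 203 anchor.** Evaluable CD patients: 0.9 × 321 ≈ 289. Pooled two-sided Z test at 0.01, 25-point difference:

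| Lower v higher rate | 1:1 | 2:1 | 1:2 |
|---|---|---|---|
| 20% v 45% | 97.9% | 96.0% | 96.4% |
| 30% v 55% | 96.2% | 93.6% | 93.9% |
| 35% v 60% | 95.9% | 93.2% | 93.3% |
| 40% v 65% | 95.9% | 93.3% | 93.2% |
| 50% v 75% | 97.0% | 95.0% | 94.6% |
| 60% v 85% | 98.8% | 97.9% | 97.6% |

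Over lower-group rates from 5% to 70% and all three ratios, power does not fall below about 93%. In the least favourable cells (35% v 60% at 2:1, 40% v 65% at 1:2), 203 patients would give only about 74%, not the planned 80%. The 93% is therefore a cautious floor.

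**Step 6: the same surplus as a detectable difference.** 0.25 × √(203/321) = 0.199, so about 20 points with 80% power.

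**Step 7: what would count as slight?** By the Step 4 formula (two-sided), 82% power corresponds to about 212 CD patients, 85% to about 227 and 90% to about 259. All are well short of 321.

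**Step 8: sensitivity to the share.** With 535 held fixed and UC/IBD-U at 45% instead of 40%, CD would number 0.55 × 535 ≈ 294 and power would be about 94%.

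**The case against.** The best defence is that nothing numerical in the section is false. It gives no CD power figure. It says 80% was planned and that CD will exceed it, and both are true. Only an adverb is at issue. The discrepancy runs in the safe direction, type I error is untouched, and no analysis changes. *Analysis and statistical methods* also promises 95% confidence intervals for the group proportions, which help a reader judge a null result better than planned power does. And 535 is a minimum, so power at that size may not describe the final cohort.

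Most of this stands, and it limits the severity. It also disposes of several stronger readings that a reader might infer:

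- *That a stated CD power is wrong.* None is stated beyond the qualitative description.
- *That the 25-point effect is wrong for CD.* It is a target chosen by design, framed as that difference or more. A larger group does not falsify a target; it meets it with more power.
- *That 535 is wrong.* UC/IBD-U is the limiting group and correctly drives the total.
- *That the surplus ought to be spent on a stricter alpha, or that power at 1000 patients must be tabulated.* These are preferences, and a condensed article need not do either.

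A single figure of 96% would also claim more precision than the inputs allow, because remission rates and sidedness are not given and the 40% share is approximate. A range with its assumptions is the fair form.

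What the defence does not rescue is the word itself. Raising power from 80% to 93% or more cuts the type II error from 20% to 7% or less. A fuller analysis plan would not make the sentence accurate, because the sentence is contradicted by figures in its own paragraph.

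**Conclusion.** The point holds as a correction of wording, at minor severity. With about 321 CD patients against 203 required, CD power for a 25-point difference at alpha 0.01 is about 96% if 203 is accepted as giving 80%. It is about 93% or more by direct calculation over lower-group remission rates of 5% to 70% and ratios of 2:1 to 1:2. Calling this slight materially understates it: the type II error is about 4% to 7%, where the sentence suggests nearly 20%.

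The result assumes a 60% CD share of 535, the stated 10% loss and a two-sided test; the one-sided reading changes it by less than one point. The sample size and the target difference stand as the protocol gives them, and the primary analysis is not endangered.

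**What to change.** Replace the sentence on CD power with, for example: *With 535 patients and about 60% CD, about 321 patients will have CD, giving roughly 93–96% power for a 25-point difference at alpha 0.01, or 80% power for about 20 points.* State beside it the remission rates and sampling ratio assumed, and whether the test is two-sided, so that the range can be reproduced. If the rates behind the 203 are on file, use those and give the single resulting figure.

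The cost is one or two sentences. The design, the sample size and the analysis stay as they are.

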### Data collection and management

Data are collected in REDCap, a secured database, by using online case report forms (CRFs). CRFs are based on the dataset of the Canadian inception cohort by the Canadian Children Inflammatory Bowel Disease Network (CIDsCaNN) and adjusted to the needs of this study. A monitor performs remote (digital) monitoring for each participating centre yearly after inclusion. The coordinating investigator runs consistency checks on a monthly basis and produces queries to be resolved by the local investigators. To secure accurate comparison of biomarkers in tissue specimens obtained from different centres, highly reproducible sample preparation is required across all centres participating in this study. Therefore, all aspects of sample acquisition and all reagents will be strictly regulated, and sample quality will be tightly monitored.

### Analysis and statistical methods

Data analysis will be performed with SPSS V.26 or higher for Windows and R version 3.6 or higher (R Foundation for Statistical Computing, Vienna, Austria). Descriptive statistics will be computed overall and per disease (CD and UC). Phenotypic grouping will be performed according to specific disease characteristics (eg, age of onset, disease localisation and disease behaviour). Next to this, patients will be categorised according to treatment categories. The appropriate descriptive statistics will be used to summarise the demographic characteristics. The primary outcome will be analysed using a 2-proportion Z test for the comparison of the different groups in our sample, using a stricter confidence level of 0.01 per Bonferroni correction. All proportions will be summarised per group, and 95% CIs will be provided. The important factors from the univariate analysis will be used to build a generalised linear model with a logit link function. This will be a multiple analysis of the effects that the selected factors and covariates have on the outcome of clinical remission. The final model will also include interaction terms, if necessary, and will be optimised based on fit diagnostics and residual analysis. The same approach will be used for the secondary outcomes of clinical remission. We will use a mixed-effects linear model to study the effects of the predictors on the disease activity index over time, taking into account the non-independence between the observations due to the repeated measurements from each patient. For the additional long-term secondary outcomes that have a time-to-event nature, we will use Kaplan-Meier curves to summarise the effects of the categorical factors on the outcome. This will be used to build a Cox regression model with the important factors and covariates that have a significant effect on the time and frequency of the events as defined in the outcomes section.

Similar methods will be used for the analysis of the exploratory outcomes. For these outcomes, propensity scores and multivariate methods are required, in particular for the immunological data, including principal component, factor and cluster analysis. Incidences of serious adverse events (SAE) and the SAE rate per 100 patient-years will be calculated. Missing data analysis will be performed based on the missing at random or missing completely at random mechanisms. Emerging patterns will be thoroughly examined.

### Study status

The first study participant was recruited in 2017. The number of included patients up until February 2020 is 400. Enrolment is expected to be completed by the end of 2021.

### Patient and public involvement

Patients and/or the public were not involved in the initial development, or conduct, or reporting or dissemination plans of this research. However, the French patient charity AFA Crohn, RCH, France, was involved in the final study design and critically reviewed and commented on main aspects of the trial.

## Discussion

The PIBD-SETQuality inception cohort is a unique study, being the first cohort in its size including patients with PIBD from European and Asian countries. The homogeneous collection of data from several different countries in one cohort enables comparison of disease phenotype and treatment paradigms between countries and continents. The hypothesised role of environmental factors in the pathogenesis of PIBD might thus be assessed within this cohort. In addition, being a cohort with real-world data, this study will complement data derived from clinical trials and provide insight in drug use in everyday practice and the related international differences.

The main outcome of this study will be the prediction of a complicated disease course and response or non-response to therapy. One of the important strengths of this study is the collection of biomaterial in therapy-naïve patients. Studies assessing immunological biomarkers in patients with PIBD are scarce and even lacking in therapy-naïve patients. The prospective set-up of this study will reveal whether immunological biomarkers in PIBD change overtime and in response to therapy. In addition, these biomarkers can be correlated to the clinical data. Besides finding predictive factors of a complicated disease course and response to therapy within this real-world cohort, we will also use this cohort to examine and possibly validate previously reported findings from other studies such as the GROWTH CD study.^37 38^
